### **Withdrawal from study**

1. Refuse further participation (withdrawal of informed consent).
2. Concomitant disease or exacerbation of background disease that may be unsafe for the patient to continue in the study (considered as an adverse event).
3. Protocol deviation that would prevent further participation in the study
4. Lost to follow-up.

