**Gastrointestinal side effects: SRL and MMF pharmacokinetic interaction:** These adverse events are mostly related to MMF toxicity although SRL was also described as a cause of intestinal ulcerations and diarrhoea. In fact, painful oral ulcers are frequently reported in patients treated with SRL-MMF. On the other hand, Kreis et al. reported higher incidence of diarrhoea in SRL-MMF than in CsA-MMF (38% vs. 11%). Interestingly, these authors' pharmacokinetic studies showed that, with an equivalent MMF dose, MPA trough levels were significantly higher in SRL- than in CsA-treated patients. Elsewhere, a pharmacokinetic explanation of these findings was provided: that CsA decreases biliary excretion of MPA glucuronide by a mechanism that involves inhibition of multidrug resistance-associated protein 2, blocking an important mechanism for maintaining MPA concentration. In a recent paper, Cattaneo et al. found that SRL but not CsA treated patients showed a second peak consistent with the enterohepatic recirculation of MPA. The result is that nearly half a dose of MMF is usually required to maintain adequate MPA concentration in CsA-free regimes. However, it should be pointed out that the value of trough MPA concentration for MMF therapy still has to be determined.

**Lymphocele and wound-healing complications:** The use of SRL and MMF has been described as causing cicatrization problems. This kind of adverse event is poorly defined in most studies and its incidence could range between 5% and 40%. However, all immunosuppressive agents inhibit to some extent wound healing, especially steroids. Although controversial, these results suggest that in the SRL-MMF combination, experience is critical in making refinements that lead to a significant improvement in the postsurgical period. All these observations raise the question of when to start SRL after transplant surgery.

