FoxP3+ T regulatory cell population will be analyzed at baseline, and at 1, 3 and 6 months after enrolment. By flowcytometry using anti-human allophycocyanin (APC) conjugated-CD4 antibodies, phycoerythrin (PE)-Cy7 conjugated-CD25 antibodies (BD Biosciences) and Alexa-fluor 488 conjugated-FoxP3 antibodies (BD Biosciences) on BD FACS Aria II (BD Biosciences). A total of 20000 events will be acquired, and CD25+ FoxP3+T cells will be counted using FACS DIVA 6.0.

1: 1 randomization will be done with the help of a computer generated random number table, and allocation concealment will be achieved by opaque sequentially numbered sealed envelopes. The response of the patient to the therapy will be in terms of renal function assessment. The primary analysis will be two-sided independent sample t-test for difference of means for GFR estimation by MDRD method.

A sample size of at least 25 patients per treatment arm will provide at least 80% power based on the assumption of an effect size (difference of GFR estimates between two treatment arms) of 8 mL/min and S.D. as 10 mL/min

The secondary endpoints will be:

- Acute rejection
- Patient and graft survival at 6 months,
- Incidences of hyperlipidemia, NODM, hypertension and infectious complications
- Regulatory T-cell population

All patients will be followed up at 15, 30, 60, 120 and 180 days. All investigations required to determine the primary and secondary end points will be performed. Sirolimus levels will be determined at 5, 12, 30, 60 and 120 days in patients randomized to sirolimus arm whereas those on tacrolimus will have measurements at 30, 60 and 120 days.

The target trough levels are as follows:

- Sirolimus: 8-15ng/ml
- Tacrolimus: 8-10 ng/ml upto mo 3, 6-8 ng/ml thereafter
- Cyclosporine: 200-300 ng/ml upto mo 3, 150-250 ng/ml thereafter

All unexplained episodes of graft dysfunction will be investigated by biopsy. Acute rejection will be treated as per standard protocol.

Variables will be presented as mean  $\pm$  SD and categorical variables as percentages. Appropriate statistical studies will be used for analysis of results. Two-tailed P-value  $<0.05$  will be considered significant.

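### The withdrawal rule does not separate stopping treatment from leaving the study and makes no provision for GFR after withdrawal, so the GFR comparison may be biased in an unknown direction

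*Protocol*

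**What the plan says.** The Protocol section Withdrawal from study gives four grounds. Two are unavoidable: withdrawn consent and loss to follow-up. The other two are decisions made about the patient:

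- "Concomitant disease or exacerbation of background disease that may be unsafe for the patient to continue in the study (considered as an adverse event")
- "Protocol deviation that would prevent further participation in the study"

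Both speak of leaving the study. Neither the section nor the rest of the protocol treats stopping the assigned drug as a separate event, and nothing is said about outcome data after withdrawal.

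STUDY METHOD says that all subjects are assessed through to the end of the 6-month study period, that all patients have visits up to day 180, and that the investigations needed for the endpoints are done. It does not say whether this includes patients who have been withdrawn. The design is open label. On the analysis it says: "The primary analysis will be two-sided independent sample t-test for difference of means for GFR estimation by MDRD method". That sentence names neither a time point nor an analysis set; month 6 is inferred from the study period.

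In STUDY VISIT PLAN, the blood-test row, which includes serum creatinine, is marked at baseline and then only at visits 4 and 5 (days 120 and 180).

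**The concern.** A t-test uses only patients who have a GFR value. If withdrawal ends data collection, the comparison is made among those who remained, and the balance created by randomisation is no longer guaranteed. An SAP can choose analysis sets and missing-data methods, but it cannot restore a creatinine that was never drawn. The collection rule therefore belongs in the protocol.

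Three features make the question more than formal:

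- Whether a deviation prevents further participation is a judgement made with the arm known.
- One arm continues a drug that its patients already take, while the other starts a new one, so withdrawal could differ between arms.
- On the visit table, a patient withdrawn before the day-120 visit has no scheduled post-baseline creatinine, which leaves little to model from.

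The same patients could also be missing from the 6-month counts of rejection and of patient and graft survival.

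**Working it through.** **1. The texts side by side.** Withdrawal from study removes some randomised patients from the study. STUDY METHOD follows all patients to day 180. Either the second statement covers withdrawn patients, and the withdrawal section should say so, or it does not, and their day-180 GFR is not planned. The text does not settle which.

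**2. The plan's own figure.** Inputs from STUDY METHOD: "effect size (difference of GFR estimates between two treatment arms) of 8 mL/min and S.D. as 10 mL/min", two-sided 5% level, 1:1 allocation. The stated result is: "A sample size of at least 25 patients per treatment arm will provide at least 80% power".

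- n per arm = 2 × (1.960 + 0.842)² × 10² / 8² = 24.5, rounded up to 25.
- Power at 25 per arm is 80.7% (normal approximation) or 79.1% (exact noncentral t). The stated figure is reproduced.
- The PATIENTS section plans 60, or 30 per arm. With all 30 per arm followed, power is 87.3% (normal approximation) or 86.1% (exact t).
- 60 against 2 × 25 leaves room for 10 losses (10/60 = 16.7%). The protocol does not call this a dropout allowance. After 10 losses, exact-t power is 79.1% if 25 remain in each arm and 77.5% if 20 and 30 remain.

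Power is therefore not the main issue; possible bias is.

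**3. Bias formula.** Let w be the share of an arm withdrawn without a day-180 GFR, C the completers' mean, and g the amount by which the withdrawn patients' unobserved GFR falls below C. The mean of the whole arm is (1 − w)C + w(C − g) = C − wg, so completers overstate the arm by wg. With the same g in both arms:

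bias in (sirolimus − CNI) = (w_SRL − w_CNI) × g

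**4. Illustration.** The protocol gives neither w nor g, so every value below is an assumption. The last column is the chance of a significant two-sided result when there is no true difference (SD 10). Completers are 24 and 28 for 20% versus 5% (30 × 0.95 = 28.5, taken as 28), and 25 and 30 for 16.7% versus 0%.

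| w_SRL vs w_CNI | g (mL/min) | Bias (mL/min) | Rejection rate under no difference |
|---|---|---|---|
| equal | any, same in both arms | 0 | 5% |
| 20% vs 5% | −10 | 0.15 × (−10) = −1.5 | not calculated |
| 20% vs 5% | 5 | 0.15 × 5 = +0.75 | 5.8% |
| 20% vs 5% | 10 | 0.15 × 10 = +1.5 | 8.3% |
| 20% vs 5% | 20 | 0.15 × 20 = +3.0 | 18.5% |
| 16.7% vs 0% | 10 | 0.167 × 10 = +1.7 | 9.3% |

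If the CNI arm lost more patients, every sign would reverse. Equal withdrawal gives zero only if g is also equal: the general form is w_SRL × g_SRL − w_CNI × g_CNI.

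**The case against.** The best reply is that the protocol nowhere says that the day-180 creatinine is omitted after withdrawal, and that STUDY METHOD says all patients are followed to that day. On this view the withdrawal section is only unclear. Part of this stands: loss of data is a risk, not a stated fact. But a general sentence about all patients does not plainly reach those whom another section has taken out of the study, so the two still have to be reconciled.

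A reader might also draw stronger conclusions that the documents do not support:

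- **That only completers are analysed.** No completer or per-protocol set is stated. Analysis sets and missing-data rules may be in an SAP that is not shown.
- **That patients who do not tolerate sirolimus, or who return to CNI, are withdrawn.** Neither is a listed ground. The disease ground names concomitant or background disease, and the deviation ground covers only deviations that prevent participation.
- **That deaths and graft losses are dropped.** They are not withdrawal grounds, and patient and graft survival is a secondary endpoint. How they enter the GFR analysis is usually an SAP matter.
- **That the bias favours sirolimus.** The literature review does report "higher incidence of diarrhoea in SRL-MMF than in CsA-MMF (38% vs. 11"%). That figure comes from a trial that the section on de novo CNI avoidance describes as using doses much higher than those now recommended. This trial enrols patients at least 2 months after transplant and excludes severe diarrhoea. The 20–45% figure for leukopenia and thrombocytopenia has no CNI comparator. Neither figure is a withdrawal rate. The section on switching in the maintenance phase also cites a conversion trial with fewer deaths and a trend to less rejection and graft loss.

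**Conclusion.** The point holds as a gap in data collection that may bias the primary comparison. It does not hold as a demonstrated bias. The text establishes three things: randomised patients can leave the study on two discretionary grounds, no outcome collection is provided for them, and the section is not reconciled with the statement that all patients are followed.

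Direction and size are unknown. Under the assumed 20% versus 5% withdrawal, the bias runs from −1.5 to +3.0 mL/min for g from −10 to +20. At the upper end, that is 3.0/8 = 38% of the design difference. If withdrawal and g are equal between arms, or if g is zero, there is no bias. These results rest on the assumed rates and gaps, on the same g in both arms, and on withdrawn patients having no day-180 value. The change is worth making because it is cheap and cannot be made afterwards.

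**What to change.** - Amend Withdrawal from study so that an adverse event, a protocol deviation or a change of assigned treatment does not by itself end follow-up. Only withdrawn consent to follow-up or loss of contact should do so. This concerns data collection and leaves clinical decisions about treatment as they are.
- Collect day-180 creatinine, and rejection, graft and survival status, on every other randomised patient, and compare by allocated arm.
- State in STUDY METHOD that the assessments to day 180 include patients who have stopped or changed the assigned treatment, so that the two sections agree.

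Rank-based, imputed or on-treatment analyses can be left to the SAP.

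The cost is a wording change and one routine creatinine per affected patient. The small downside is that the estimate then includes patients who changed treatment, so the effect may be diluted.

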### **STUDY METHOD**

This will be an open label, prospective, randomized, two arm study to be conducted in renal transplant recipients who have undergone renal transplant >2 months prior to enrollment. Renal transplant recipients who had undergone live donor renal transplantation and are on CNI based maintenance regimen will be screened for inclusion and exclusion criteria. Informed consent will be taken after explaining the objectives and procedures of the trial from all the patients who agree to participate in the study. Subjects who satisfy all inclusion and exclusion criteria will either continue with existing CNI regimen or converted from CNI based regimen to sirolimus with CNI withdrawal.

At baseline patient's past, family, medical, transplant and medication history will be enquired and relevant findings will be recorded in the CRF. Patient's general and physical findings will be recorded. Baseline laboratory investigations including CBC, electrolytes, fasting blood sugar, renal profile, SGOT, SGPT, Lipid profile, urine analysis and 24 hrs urine test for urine proteins will be done and recorded. Baseline and subsequent GFR will be calculated by MDRD method. CNI dose and blood levels of all the patients will be recorded at baseline. Subsequently the patients will be randomized either to CNI group who will continue with existing dose or to Sirolimus group. Patients allocated to Sirolimus group, will be initiated

with a loading dose of 6mg for 2 days and later the dose will be adjusted to achieve a blood level of 8-15ng/ml. The CNIs in sirolimus group will be discontinued 12 hrs prior to initiating Sirolimus. Later, in CNI or sirolimus group the dose of individual drugs will be titrated as per target blood level and clinical response. Concomitant immunosuppressants like Mycophenolate mofetil (MMF) and steroids will be continued as per the clinical practice. All the drugs for any pre-existing or co-existing illness will be allowed unless those drugs are contraindicated. All the subjects will be assessed at regular intervals and at the end of study period of 6 months. Relevant laboratory investigations will be done at defined intervals and all the investigations done at baseline will be repeated at the end of study period.

FoxP3+ T regulatory cell population will be analyzed at baseline, and at 1, 3 and 6 months after enrolment. By flowcytometry using anti-human allophycocyanin (APC) conjugated-CD4 antibodies, phycoerythrin (PE)-Cy7 conjugated-CD25 antibodies (BD Biosciences) and Alexa-fluor 488 conjugated-FoxP3 antibodies (BD Biosciences) on BD FACS Aria II (BD Biosciences). A total of 20000 events will be acquired, and CD25+ FoxP3+T cells will be counted using FACS DIVA 6.0.

1: 1 randomization will be done with the help of a computer generated random number table, and allocation concealment will be achieved by opaque sequentially numbered sealed envelopes. The response of the patient to the therapy will be in terms of renal function assessment. The primary analysis will be two-sided independent sample t-test for difference of means for GFR estimation by MDRD method.

A sample size of at least 25 patients per treatment arm will provide at least 80% power based on the assumption of an effect size (difference of GFR estimates between two treatment arms) of 8 mL/min and S.D. as 10 mL/min

The secondary endpoints will be:

- Acute rejection
- Patient and graft survival at 6 months,
- Incidences of hyperlipidemia, NODM, hypertension and infectious complications
- Regulatory T-cell population

All patients will be followed up at 15, 30, 60, 120 and 180 days. All investigations required to determine the primary and secondary end points will be performed. Sirolimus levels will be determined at 5, 12, 30, 60 and 120 days in patients randomized to sirolimus arm whereas those on tacrolimus will have measurements at 30, 60 and 120 days.

The target trough levels are as follows:

- Sirolimus: 8-15ng/ml
- Tacrolimus: 8-10 ng/ml upto mo 3, 6-8 ng/ml thereafter
- Cyclosporine: 200-300 ng/ml upto mo 3, 150-250 ng/ml thereafter

All unexplained episodes of graft dysfunction will be investigated by biopsy. Acute rejection will be treated as per standard protocol.

Variables will be presented as mean  $\pm$  SD and categorical variables as percentages. Appropriate statistical studies will be used for analysis of results. Two-tailed P-value  $<0.05$  will be considered significant.

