### **INCLUSION CRITERIA**

- Willing to sign informed consent
- Adult renal transplant recipients of either sex over the age of 18 years
- Undergone denovo live donor renal transplantation at least 2 months prior to enrolment
- Receiving CNI based maintenance regimen after transplantation
- Serum creatinine  $\leq 1.2$ mg/dl and proteinuria  $< 800$ mg/day

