**Support:**

The study drugs (sirolimus, tacrolimus and cyclosporine) will be provided by Biocon India, Bangalore.

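### Randomisation and the primary t-test both ignore which CNI a patient takes, although it is known at entry: a low-severity, cheaply removed source of chance imbalance

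*Protocol*

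**What the plan says.** The inclusion criteria set the background treatment only at class level: "Receiving CNI based maintenance regimen after transplantation". Two CNIs are in use, since the Support section states "The study drugs (sirolimus, tacrolimus and cyclosporine) will be provided". STUDY METHOD gives each its own trough target: "Tacrolimus: 8-10 ng/ml upto mo 3, 6-8 ng/ml thereafter" and "Cyclosporine: 200-300 ng/ml upto mo 3, 150-250 ng/ml thereafter". Patients on either drug form a single CNI group.

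STUDY METHOD has CNI dose and blood level recorded at baseline, with randomisation afterwards. On allocation it says "1: 1 randomization will be done with the help of a computer generated random number table", concealed in sealed opaque envelopes. It names no stratification factor and no blocking. The primary analysis is a two-sided independent-sample t-test on MDRD GFR, with no covariate.

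The Adverse events section, in its paragraph on gastrointestinal effects, describes an interaction with MMF for one of the two drugs: "CsA decreases biliary excretion of MPA glucuronide by a mechanism that involves inhibition of multidrug resistance-associated protein 2". It adds that "nearly half a dose of MMF is usually required to maintain adequate MPA concentration in CsA-free regimes". It describes no corresponding effect for tacrolimus. On MMF within the trial, STUDY METHOD says "Concomitant immunosuppressants like Mycophenolate mofetil (MMF) and steroids will be continued as per the clinical practice", without distinction by CNI.

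**The concern.** The drug that is withdrawn in one arm and continued in the other is either tacrolimus or cyclosporine. On the protocol's own account, stopping cyclosporine also changes the handling of mycophenolic acid, and it says nothing similar for tacrolimus. CNI type is therefore a plausible prognostic factor, and possibly a modifier of the conversion effect. It is known before the envelope is opened.

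Neither the allocation nor the named primary test uses it. In a trial of 60, a plain 1:1 list can leave the arms visibly different in CNI mix. If GFR at 6 months differs by CNI, part of the observed arm difference would then reflect that mix, and the unadjusted test would not remove it.

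**Working it through.** **The plan's own figure.** Difference 8 mL/min, SD 10 mL/min, two-sided alpha 0.05, power 80%:

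n per arm = 2 × (1.960 + 0.842)² × 10² / 8² = 24.5, so 25. This reproduces the protocol's 25 per arm (power 80.7% by the normal approximation). With the t distribution, 25 per arm gives 79.1%. The stated total of 60 means 30 per arm if split equally, with power 86.1%.

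**Inputs the protocol does not give.** These are the share of patients on cyclosporine (assumed 20%, 30% or 50%) and the difference in 6-month GFR between the CNIs (assumed 5-8 mL/min). Both are assumptions shown as ranges.

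**Step 1: how often the arms differ.** With two arms of 30 and K cyclosporine patients among 60, the number in one arm is hypergeometric:

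| Assumed share | K | P(difference ≥ 10 points) | P(difference ≥ 20 points) |
|---|---|---|---|
| 20% | 12 | 33% | 10% |
| 30% | 18 | 40% | 16% |
| 50% | 30 | 44% | 20% |

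At a 10% share (K = 6) the chance of 20 points or more is only 2%.

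**Step 2: what a 20-point imbalance does to the GFR difference.**

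- Gap present in both arms at 6 months: shift = 0.20 × gap, so 0.20 × 5 = 1.0 and 0.20 × 8 = 1.6 mL/min.
- Gap present only while the CNI continues: only the control arm matters. It lies about 10 points from the overall mix, so the shift is 0.10 × 5 = 0.5 to 0.10 × 8 = 0.8 mL/min.

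**Step 3: compare with the precision.** Standard error = 10 × √(2/30) = 2.58 mL/min. The shift is 1.0/2.58 = 0.39 to 1.6/2.58 = 0.62 standard errors in the first case, and 0.5/2.58 = 0.19 to 0.8/2.58 = 0.31 in the second. Against the 8 mL/min design effect it is 12.5-20%, or 6-10%.

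**Step 4: error rates given such a shift, 30 per arm (noncentral t).**

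| Shift (mL/min) | Type I error | Power if the shift goes against sirolimus |
|---|---|---|
| 0.5 | 5.4% | 81.5% |
| 1.0 | 6.7% | 76.0% |
| 1.6 | 9.4% | 68.4% |

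**Step 5: average over all randomisations.** This was simulated at 25 per arm, with 40,000 trials per scenario, total SD held at 10, cyclosporine share 20% or 50%, and the gap present in both arms. The plain t-test has type I error of 4.9-5.1%. Adding CNI type to the model raises power from about 79.4% to 80.0-80.9% for a 5 mL/min gap, and from 78.6-79.2% to 85.2-88.6% for a 10 mL/min gap.

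**The case against.** Unstratified randomisation is valid. Chance imbalance in any covariate is already allowed for in the standard error, and Step 5 confirms that the 5% level holds on average. This stands, and it is why the point is one of efficiency and of protecting the realised trial.

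The size is assumed throughout. This also stands. A gap of 5-8 mL/min is 0.5-0.8 of the planned SD, and the entry limit of 1.2 mg/dl on serum creatinine narrows differences at baseline. Separate trough targets are simply how two drugs are monitored and do not show a GFR difference. The MMF passage concerns mycophenolic acid exposure and adverse events, not GFR. Its silence on tacrolimus does not establish that there is no interaction. The STUDY VISIT PLAN also schedules adjustment of concomitant drugs at visits 1 to 5, so MMF need not stay fixed after conversion.

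Pooling the CNIs matches a class-level question, and the protocol gives no ground for ranking CNI type above, say, baseline GFR as a stratification factor. That is fair. CNI type is proposed because it defines what is withdrawn or continued and is already recorded.

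A statistical analysis plan, not shown, could add a covariate or results by CNI. It could not stratify the allocation, and the protocol already names an unadjusted test as primary.

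A reader might go further and infer that the result could not be attributed to conversion, or that effects by CNI cannot be shown without stratification. The documents support neither. The first could be said of any unstratified prognostic factor. The second fails because the CNI is recorded at baseline, so results by CNI can be tabulated anyway; the number of patients is what limits a reliable interaction test.

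**Conclusion.** The point holds as a low-severity improvement. Allocation and the primary test both ignore a plausible prognostic factor that is known at entry. With 30 per arm and an assumed cyclosporine share of 20-50%, the arms differ by at least 20 points in about 10-20% of randomisations. Under an assumed gap of 5-8 mL/min, such an imbalance moves the GFR difference by 1.0-1.6 mL/min, or 0.5-0.8 mL/min if the gap disappears once the CNI is stopped.

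It would be tempting to say that imbalance could account for a quarter of the 8 mL/min design effect. That figure needs an even CNI split, a 25-point imbalance at the edge of the 95% range, the largest assumed gap (0.25 × 8 = 2.0 mL/min), and a gap that persists in the sirolimus arm after withdrawal. The documents do not support stacking these. If one CNI is rare, or the two drugs carry similar GFR, the effect is small.

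**What to change.** In STUDY METHOD, replace the single list with two concealed envelope sets, one for patients entering on tacrolimus and one for those on cyclosporine. Generate each 1:1 in permuted blocks of randomly varied size, and do not disclose the sizes to recruiting staff. The variation matters because the trial is open label, and small fixed blocks would let staff guess upcoming allocations. Replace the plain t-test by a linear model for 6-month MDRD GFR with treatment and CNI type at entry. Show the GFR difference within each CNI group descriptively.

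The total stays at 60, and no extra patients, visits or measurements are needed. The costs are a second list and envelope set, a possible inequality of one or two patients between arms from incomplete final blocks, one degree of freedom in the analysis, and allocation slightly more predictable than with an unblocked list.

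### The primary GFR comparison is an unadjusted t-test although baseline GFR is in hand for every patient, which gives up precision and protection against chance baseline imbalance

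*Protocol*

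**What the plan says.** All of this stands in the Protocol under STUDY METHOD unless another section is named.

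- **Primary analysis:** "The primary analysis will be two-sided independent sample t-test for difference of means for GFR estimation by MDRD method". No covariate is named. The sentence does not say whether the variable is the final GFR or its change from baseline.
- **Baseline value:** "Baseline and subsequent GFR will be calculated by MDRD method". The baseline work-up is described first, and allocation follows it: "Subsequently the patients will be randomized either to CNI group who will continue with existing dose or to Sirolimus group". STUDY VISIT PLAN lists serum creatinine at visit 0.
- **Allocation:** 1:1, and "randomization will be done with the help of a computer generated random number table". No stratification or other balancing on baseline GFR is described.
- **Sample size:** "A sample size of at least 25 patients per treatment arm will provide at least 80% power", assuming an "effect size (difference of GFR estimates between two treatment arms) of 8 mL/min and S.D. as 10 mL/min". PATIENTS sets the total at 60, which is 30 per arm.
- **Level:** two-tailed 0.05.

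The remaining analysis text is a general statement that suitable methods will be used. It does not add an adjusted primary analysis.

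**The concern.** The protocol does not leave the primary method to a later plan. It commits to a test that, read as a comparison of follow-up GFR, makes no use of a measurement the trial already takes. Baseline GFR is recorded before randomisation, on the same scale and in the same graft, so it is a legitimate covariate and can be expected to correlate with the 6-month value.

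Two things are at stake in a trial of this size. First, simple randomisation of about 25 to 30 patients per arm can leave the arms several mL/min apart at baseline, and the unadjusted difference carries part of that gap with it. Second, the share of outcome variance that baseline explains stays in the error term, so the confidence interval is wider and the power lower than the same patients could give.

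**Working it through.** **Inputs from the Protocol (STUDY METHOD, PATIENTS).** Difference 8 mL/min, SD 10 mL/min, two-sided alpha 0.05, stated minimum n = 25 per arm, planned n = 30 per arm (60 in total, 1:1).

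**Assumptions not in the documents.** Baseline SD equals 10 mL/min. The correlation r between baseline and 6-month GFR is 0.3, 0.5, 0.6 or 0.7.

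**1. The plan's own figure.** Normal approximation: n = 2 × (1.960 + 0.842)² × (10/8)² = 24.5, so 25 per arm, with power 80.7% at 25. The noncentral t (noncentrality 8 / (10 × √(2/n)), 2n − 2 df) gives 79.1% at 25 per arm and 86.1% at 30. The stated sample size reproduces within rounding.

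**2. Chance baseline difference.** SE = 10 × √(2/n).

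| n per arm | SE | 95% range (±1.96 × SE) | Range limit as share of 8 | Chance of a gap of 4 or more |
|---|---|---|---|---|
| 25 | 2.83 | ±5.5 | 69% | 15.7% |
| 30 | 2.58 | ±5.1 | 63% | 12.1% |

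With equal SDs at the two times, the regression slope of follow-up on baseline is r, so a baseline gap g moves the unadjusted difference by r × g.

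- At the 95% limit with 30 per arm: 0.5 × 5.06 = 2.5 to 0.7 × 5.06 = 3.5 mL/min.
- For a gap of 4 mL/min: 0.5 × 4 = 2.0 to 0.7 × 4 = 2.8 mL/min.

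**3. Power with baseline adjustment.** Residual SD = 10 × √(1 − r²); noncentral t with 2n − 3 df.

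| r (assumed) | Residual SD | Power, 25 per arm | Power, 30 per arm |
|---|---|---|---|
| unadjusted t-test | 10.00 | 79.1% | 86.1% |
| 0.3 | 9.54 | 82.7% | 89.1% |
| 0.5 | 8.66 | 89.2% | 94.0% |
| 0.6 | 8.00 | 93.4% | 96.8% |
| 0.7 | 7.14 | 97.2% | 98.9% |

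**4. If the t-test is meant on change from baseline.** With SD 10 at each visit, the SD of change is 10 × √(2(1 − r)). Power at 25 per arm is then 64.9%, 79.1%, 87.3% and 94.7% for the same four values of r. That is below ANCOVA in every row.

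**5. If SD 10 already describes change.** The ANCOVA residual SD becomes 10 × √((1 + r)/2): 8.66 at r = 0.5, 8.94 at 0.6 and 9.22 at 0.7. Power at 25 per arm is 89.2%, 87.2% and 85.2%. The gain over 79.1% is then unchanged at r = 0.5 and smaller above it.

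**The case against.** The strongest reply is that nothing in the planned test is wrong. Under randomisation the t-test is unbiased, its standard error already allows for chance baseline imbalance, and it matches the sample-size sentence. Preferring a valid and adequately powered test to a more efficient one is not an error. This stands, and it limits the point to efficiency and to the quality of the single estimate the trial will report.

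The size of the gain is also uncertain. The documents give neither r nor the baseline SD. INCLUSION CRITERIA admits only patients with serum creatinine of 1.2 mg/dl or less, which truncates the main input to MDRD GFR and may lower both. At r = 0.3 the gain is 82.7 − 79.1 = 3.6 points at 25 per arm and 89.1 − 86.1 = 3.0 points at 30. This too stands, and is why a range is shown. Nor is it certain that baseline is ignored, since the sentence could mean change from baseline; but that reading is also less efficient than ANCOVA under the same SD.

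Three stronger readings are not supported:

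- **That chance imbalance makes the test biased or inflates type I error.** It does neither over repeated randomisation. The imbalance limit is about two-thirds of the target effect, and only r times it carries over.
- **That the trial is badly underpowered without adjustment,** because the Protocol's Renal function section quotes GFR SDs of 17 and 18. Those are iothalamate clearances at 1 month in another study, not 6-month MDRD values under this trial's creatinine limit.
- **That the unnamed visit lets the sponsor pick the better of day 120 and day 180.** No section proposes such a choice. STUDY METHOD sets a 6-month study period and repeats the baseline investigations at its end, so month 6 is the natural reading.

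**Conclusion.** The point holds as a worthwhile improvement to the primary analysis, not as a fault in validity or sample size. At the planned 30 per arm, baseline adjustment would add from 3.0 points of power (r = 0.3) to 98.9 − 86.1 = 12.8 points (r = 0.7). At the stated minimum of 25 it would add from 3.6 to 97.2 − 79.1 = 18.1 points. It would also remove the shift that a chance baseline gap puts into the reported difference.

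These figures rest on an assumed r, an assumed baseline SD of 10, and the protocol's SD being that of GFR at a single visit. If that SD is of change, the gain over the stated power is smaller for r above 0.5. The direction of the conclusion does not depend on the exact r: unless r is close to zero, adjustment gains more than the one degree of freedom it costs.

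**What to change.** Replace the primary-analysis sentence in STUDY METHOD with:

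> The primary analysis is an ANCOVA of day-180 (6-month) MDRD GFR on randomised arm with baseline MDRD GFR as covariate, at two-sided alpha 0.05, reporting the adjusted mean difference with its 95% confidence interval. The unadjusted two-sample t-test is a sensitivity analysis.

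This also states the visit and the form of the outcome. It would help to add whether the SD of 10 mL/min refers to GFR at one visit or to its change. The change needs no new data, visits or patients, and the sample size can stay as it is.
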